### Recruitment of practices

Practice recruitment and randomisation will be undertaken in two geographical areas (Bristol, West Midlands). Practices will be randomised immediately after the initial invitation mail-out to patient participants. This will help minimise the gap between patient consent and practice randomisation. We will recruit 37 practices who will participate in the same pre-randomisation initial set-up period to install the necessary software and provide training in the trial protocol and Good Clinical Practice for safety monitoring and reporting. To reduce risk of contamination, we will avoid recruitment of practices where pharmacists have the potential to work in both intervention and control practices.

### Recruitment of patient participants

Eligible patient participants will be identified by practices after protocol training but before randomisation. All potentially eligible patients meeting the inclusion criteria will be proactively identified using a bespoke informatics tool. This tool will search the GP electronic records to identify those patients who may benefit from the intervention, due to the presence of both multiple medications and potentially inappropriate prescribing. A computer-generated random sample of 300 potential patient participants will be screened by a GP or pharmacist for the exclusion criteria. Based on pilot work, screening resulted in an average exclusion rate of 23%, with subsequent patient acceptance rate of 23% (excluding reminder invitations); screening 300 potential participants is thus expected to provide sufficient recruitment (i.e. 50 participants), particularly when reminder invitations are included. Patients identified as eligible after screening will then be contacted in writing by post, with an invitation letter, participant information leaflet, consent form and baseline questionnaire (
*Extended data*, Appendix 2
^
18
^) sent by practices. Those patients willing to participate will be required to return a signed and dated postal consent form; consent will be unwitnessed. If recruitment rates are inadequate after 28 days, a reminder invitation pack will be sent to a random sample of non-responders (number of reminders will be determined by initial response rate). Eligible patients who do not respond to the reminder invitation will not be contacted further regarding the study. If patient participant numbers remain inadequate after reminders, a further case-finding and screening process will be undertaken, with numbers based on the earlier response rates.

### Randomisation and blinding

As soon as initial postal invitations have been sent by a practice, the practice will be randomised. Randomisation will be independently undertaken by computer by the Bristol Clinical Trials Unit. Randomisation will be stratified by region (Bristol, West Midlands). We will not wait for consent forms to be returned before randomising practices; however, we believe the vast majority of patients will remain blind to their practice’s randomisation status at this stage, and it is highly unlikely to influence their consent or baseline questionnaire responses. Potential patient participants sent a reminder will not be informed of the randomisation status of the practice. The study will use as an open-label design, with neither patients nor clinicians blinded to the intervention or study end points. Statistical analysis will be performed blind to practice allocation.

### Description of intervention

The intervention will take place in general practice, involving GPs and clinical pharmacists working together, drawing on the specific skills of each professional sensitive to the context of each practice. This is a complex intervention and will comprise a model for conducting a polypharmacy medication review (including structured case-finding, pharmacist-GP liaison and collaboration, and a patient-centred approach), and components seeking to enhance professional engagement (clinician training, practice feedback, financial incentives). An informatics tool integrated into GP clinical systems will help support structured case-finding, the medication review itself, and the practice feedback component (
Figure 2). Full details of the intervention are provided in the
*Extended data* (Appendix 3)
^
18
^. Practices will not be explicitly excluded from delivering non-trial medication reviews at other times to participants, if these are clinically indicated, and receipt of a non-trial review will not preclude continued participation in the trial; data on non-trial review activity will be captured for sensitivity analysis.

**Figure 2. f2:**
[figure not shown]
Schematic of IMPPP intervention.

### Usual care

Practices in the control arm will undertake their usual care for patients with polypharmacy. We anticipate this will comprise routine medication reviews, but no specific management strategy focused on polypharmacy. Control practices will be aware that the participant has consented to a trial of a polypharmacy intervention, but will not be aware of the specific aspect of potentially inappropriate prescribing that has led to the patient’s inclusion. Furthermore, changes to medications which trigger the review process are not mandated as part of the intervention. As such, the trial will not be withholding any clinical intervention targeted at the specific prescribing indicators which would otherwise have triggered a review. Control practices will not have access to the training programme, monthly feedback, computerised enhanced medication summary, or financial incentives. Some of the control practices may have access to a clinical pharmacist, whose role may include medication optimisation.

### Outcome measurements

The primary outcome will be defined as mean number of PIP indicators triggered per participant at 26 weeks following the pre-medication review eligibility check (this check occurs in both trial arms), determined objectively from coded GP electronic health records. For each consented participant, the outcome will be determined at baseline (i.e. pre-randomisation), at the pre-review eligibility check, and at 26 weeks following the pre-review eligibility check.

Secondary outcomes will be determined at the same time points as the primary outcome. Quality of life using the SF-12 instrument, and patient-reported medication adherence and treatment burden, will be ascertained using participant questionnaires. Health and care service use will be determined by a combination of GP records, national hospital utilisation data (NHS Digital Hospital Episode Statistics for Accident and Emergency attendances, in-patient and out-patient care), and questionnaire responses.

Patient demographics will be determined at baseline using participant questionnaires. Additional clinical data (e.g. medication list, recorded clinical conditions) will be extracted approximately 6-monthly using GP electronic health records.

The list of outcome measures, associated data sources, and corresponding measurement time points, is summarised in
Table 1. Participants will have the option of responding to the questionnaire either in paper form or electronically. Appendix 2 of the
*Extended data* provides a copy of the patient questionnaires
^
18
^.

Paper questionnaire data will be entered by trained staff. Single data entry will be use, with automated validation checks performed to ensure data quality, plus double-entry checking of a 10% subset of data. The primary prescribing outcome and service usage outcomes will be collected using electronic data extraction.

### Sample size calculation

We consider an average reduction in number of potentially inappropriate prescribing indicators (primary outcome) of 0.5 per participant to be clinically meaningful. Based on data on the distribution of these indicators in pilot work, the standard deviation of the average (mean) indicator count is 2.0. Previous related studies conducted by our research group have also found an intraclass correlation coefficient (ICC) of between 0.0126 (EFIPPS
^
26
^) and 0.036 (DQIP
^
17
^). Therefore, to detect a mean decrease in number of indicators triggered per participant of 0.5 in 50 participants per practice, with a power of 90% at the 5% significant level, and assuming an ICC of 0.036, we require a total of 37 practices. Due to the automated manner in which primary outcome data are captured, we expect approximately 100% follow-up; as the follow-up period is only 6 months, we expect few participants to withdraw, move away or die during this time. Even if 20% of cases are lost to follow-up, power will still be 88% at the 5% significance level with the same number of practices. Participant engagement with the medication review process in the pilot study was ≥88%.

### Statistical analysis

The analysis and reporting of this trial will be undertaken in accordance with Consolidated Standards of Reporting Trials (CONSORT) guidelines, as extended to cluster trials. The statistical analyses will follow a pre-defined Statistical Analysis Plan (SAP) agreed prior to the end of the trial. The main primary outcome comparative analyses between randomised arms will be conducted on an intention-to-treat (ITT) basis without imputation of missing data.

The main analysis will use a linear mixed effects regression model to compare number of PIP indicators triggered at 26 weeks (after the pre-medication review eligibility check) between groups as randomised, adjusted for baseline (i.e. pre-randomisation) values of the outcome, area (stratification variable), and elapsed time between baseline and post patient-facing review 26-week follow-up. A random effect for GP practice will be included to account for clustering. The result of the regression model will be presented as an adjusted difference in mean between the intervention and control arms alongside the associated 95% confidence interval and exact p-value for the comparison. If the assumptions of the regression model do not hold then transformations of the data or alternative models (e.g. zero-inflated Poisson or negative binomial regression) will be explored.

Additional sensitivity analyses of the primary outcome will include further adjustment of the main analysis for any prognostic variables strongly related to outcome (identified
*a priori* based on clinical expert opinion, e.g. age, number of medications). A further additional analysis will be performed where baseline is taken from the pre-review time-point, with adjustment for pre-randomisation outcome values. This is proposed as there is the potential for a considerable delay between randomisation and review; medication optimisation processes during this time may vary between arms (e.g. usual care may be more likely to take action to improve prescribing, as unlike the intervention arm these practices will be aware that no IMPPP review will be occurring later) resulting in differences in prescribing immediately prior to review which are unrelated to the intervention itself.

The effect of the intervention on the secondary outcomes collected at 6 months post-review follow-up will also be examined using appropriate mixed effects regression models adjusted for baseline values of the outcome being investigated, elapsed time between baseline and 26-week post-review follow-up, area (stratification variable) and including a random effect to account for clustering by practice
**.**

The sensitivity of the main analysis to the impact of missing data (where missingness is >5%) will be explored by imputing missing primary outcome data and repeating the primary analysis model using the imputed data. The imputation model will include all variables that are part of the ITT primary analysis, baseline and post-randomisation variables that are associated with missingness, and interim data on the primary outcome collected at 3 months follow-up. It is emphasised that levels of missing data are expected to be low, as the primary outcome is captured using automated processes.

Complier average causal effect (CACE) analysis using a 2-stage-least-squares (2SLS) instrumental variable (IV) approach will be used to investigate the efficacy of the intervention in reducing potentially inappropriate prescribing indicators at 6 months. The CACE methodology compares outcomes for those who “complied” with the intervention with a comparable group of “would be compliers” in the control group. CACE analysis provides an estimate of the efficacy of the intervention for comparison with the ITT estimate of the offer of the intervention, whilst respecting randomisation and avoiding biases inherent to crude per-protocol analyses. In this trial “compliance” will be defined as undergoing the face-to-face medication review. To investigate potential moderators of treatment effect, interaction terms for treatment group by age, and treatment group by multimorbidity will be added (separately) to the primary analysis model.

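### Covariates the plan itself expects to be strongly prognostic sit only in a sensitivity analysis; moving them into the primary model is a small, nearly free improvement

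*Protocol article*

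**What the plan says.** All references are to the protocol article.

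The Statistical analysis section specifies a linear mixed model for the indicator count at 26 weeks, "adjusted for baseline (i.e. pre-randomisation) values of the outcome, area (stratification variable), and elapsed time", with a random effect for practice. It then says: "Additional sensitivity analyses of the primary outcome will include further adjustment of the main analysis for any prognostic variables strongly related to outcome". Those variables are to be chosen in advance on clinical opinion. Age and number of medications are given as examples, so the list is open.

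The information is in the GP record. Table 1 gives GP records as the source of age. The Trial participants section makes five or more repeat medicines an entry criterion, and the record search that applies it runs before randomisation. Under Outcome measurements, "Additional clinical data (e.g. medication list, recorded clinical conditions) will be extracted" roughly every six months.

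The sample size section uses a difference of 0.5, an SD of 2.0 and an ICC of 0.036, and mentions no covariate adjustment.

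**The concern.** In a linear model, a baseline covariate that predicts the outcome beyond what is already adjusted for reduces residual variance and removes the effect of any arm difference in that covariate. If the trial team expects a variable to be strongly prognostic and can fix it before seeing outcomes, the usual place for it is the primary model. Here the order is reversed: the less adjusted model gives the headline estimate. If the two analyses differ, the plan takes the one with less protection as its answer.

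The design adds some weight to this. Only 37 practices are randomised, with stratification by region alone, and part of the patient recruitment takes place after the practice has been allocated. At stake are a little precision and some protection of the main estimate against case-mix differences.

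**Working it through.** **1. The plan's own figure.** Inputs from Sample size calculation: difference 0.5, "the standard deviation of the average (mean) indicator count is 2.0", ICC 0.036, 50 per practice, power 90%, significance level 5%. Two-sided testing and 1:1 allocation are assumed, as the article states neither.

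- Without clustering, n = 337 per arm.
- Design effect = 1 + (50 − 1) × 0.036 = 2.764.
- Total = 2 × 337 × 2.764 = 1,863 participants; 1,863 / 50 = 37.3 practices, against 37 stated.
- With 37 practices, the effective number per arm is (37 × 50 / 2) / 2.764 = 334.7, SE = 2.0 × √(2 / 334.7) = 0.155, and power is 89.9%.
- With 20% loss (40 per practice), the design effect is 2.404 and power is 87.3%, against 88% stated.

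The figures reproduce to within rounding, with no covariate adjustment. The stated power therefore does not rely on age or number of medicines.

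**2. Precision gained.** Let ρ be the correlation between baseline and follow-up counts, and R² the share of the remaining variance explained by the added covariates. The article gives neither, so both are assumed. The design effect is held at 2.764.

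- Residual SD = 2.0 × √[(1 − ρ²)(1 − R²)]
- SE ratio, with against without the added covariates = √(1 − R²)

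| Assumed R² | SE reduction | Power, ρ = 0 | Power, ρ = 0.5 |
|---|---|---|---|
| 0 | – | 89.9% | 96.2% |
| 1% | 0.5% | 90.2% | 96.4% |
| 2% | 1.0% | 90.4% | 96.5% |
| 5% | 2.5% | 91.3% | 96.9% |
| 10% | 5.1% | 92.6% | 97.6% |

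At ρ = 0.7, power is 99.5% before the addition and 99.5% to 99.8% after it. Across the range the gain is about 0 to 3 percentage points.

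**3. How large a chance imbalance could be.** For a standardised covariate, the SD of the arm difference is √[(4 / 1,850) × (1 + 49 × ICC)]. The covariate's own ICC is not given and is assumed.

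- ICC 0.036: SD 0.077; probability of a difference of 0.2 SD or more, about 1%.
- ICC 0.05: SD 0.086; about 2%.
- ICC 0.10: SD 0.113; about 8%.

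A chance imbalance of that size is uncommon.

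**4. Order of recruitment and allocation.**

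- Randomisation follows directly on the first mail-out, without waiting for consent forms (Recruitment of practices; Randomisation and blinding).
- If recruitment is inadequate at 28 days, reminders go out. If numbers are still short, there is more case-finding and screening (Recruitment of patient participants). Both steps therefore fall after allocation.
- Screening is by a practice clinician and several exclusions rest on judgement (Trial participants). Clinicians are not blinded (Randomisation and blinding).
- On the article's pilot rates, the first mailing yields 300 × 0.77 × 0.23 = 53.1 per practice. The binomial SD is √(300 × 0.1771 × 0.8229) = 6.6, so the chance of fewer than 50 is about Φ[(49.5 − 53.1) / 6.6] = 29%. If 50 is the threshold for action, which is an assumption, a fair share of practices would go on recruiting after allocation.

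This shows an opportunity for case-mix to differ by arm. It does not show that it will.

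**The case against.** The strongest reply is that this is an accepted choice of analysis which contradicts nothing in the article. The primary model already adjusts for the baseline value of the outcome. Indicators are triggered by prescribing, so much of the link between medicine count and outcome probably runs through that baseline. A further-adjusted analysis is planned in advance, so the dispute is only over which of two pre-specified models is called primary. The named variables are examples, and the final list is normal content for an SAP that is not shown. All of this stands, and it is why the point is minor.

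The reply on case-mix stands in part. The first sample is drawn at random by computer and screened before allocation, and reminders do not disclose the arm to patients. That does not blind the clinician who does any later screening.

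It may also be said that medication lists are described as extracted only about six-monthly, so complete pre-randomisation values are an inference. That is fair, but a medicine count is needed for the eligibility search, and the baseline indicator count already in the model comes from the same records.

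Three stronger readings are tempting and are not supported:

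- **That the test's error rate is inflated.** That follows only if a sizeable imbalance is imposed first. Averaged over randomisation, leaving out a covariate does not bias the estimate or inflate the test, and a chance difference of 0.2 SD is uncommon (step 3).
- **That the precision loss is large.** An 11% fall in SE would need R² = 1 − 0.89² = 0.21 after baseline adjustment. Nothing in the article supports that.
- **That the moderator models lack main effects**, because "interaction terms for treatment group by age, and treatment group by multimorbidity will be added (separately) to the primary analysis model". This is ordinary shorthand, and the article does not say that main effects are left out.

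**Conclusion.** The point holds as a minor, nearly free improvement. The plan puts variables it expects to be strongly prognostic into a sensitivity analysis, so the primary estimate is somewhat less precise and less protected against case-mix imbalance than the collected data allow.

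The size cannot be derived from the article. On assumed R² values of 1% to 10%, the SE would fall by about 0.5% to 5%, with power rising by at most about 3 points. This assumes that the design effect is unchanged.

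The main result is not in danger: the design reaches its stated power without the adjustment, baseline count and the planned further-adjusted analysis already give protection, and randomisation deals with chance imbalance on average. Post-allocation recruitment by unblinded practices makes differential case-mix possible, and that is the better reason for the change.

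**What to change.** Before any outcome data are seen:

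1. Replace the examples with a closed list: age and number of repeat medicines, taken from the pre-randomisation GP record extract.
2. Include both in the primary linear mixed model with baseline indicator count, area, elapsed time and the practice random effect.
3. Report the model without them as the sensitivity analysis.

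The change is about one sentence. It needs no new data collection, and it should lose no participants if both values are taken from the records that supply the baseline indicator count. The cost is a slightly longer primary model: two more fixed effects with about 1,850 participants (37 × 50). Made after outcomes are known, the same switch would look data-driven, so timing matters. Adjustment covers only the measured covariates and would not remove selection on anything else.

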### Patient and Public Involvement

Patient input informed the design of this study. Two lay representatives will sit on the trial steering committee, and a lay advisory group will provide additional input, including interpretation of process evaluation findings, input into educational practice and patient-facing materials, consideration of ethical and regulatory aspects, identification of non-academic routes for dissemination and contribution to wider public materials.

### Safety reporting

Given the nature of participants in the IMPPP trial (older individuals with polypharmacy and therefore likely with multimorbidity), new diagnoses, hospital admissions and death are to be anticipated. An independent Data Monitoring Committee (DMC) will be established to assess trial safety and efficacy, consisting of three independent academic members including two statisticians and a clinician with relevant interests. Serious adverse events will be monitored, recorded and reported in accordance with the Good Clinical Practice (GCP) guidelines and the Sponsor’s Research Related Adverse Event Reporting Policy. Adverse events may be reported by participant or investigator, and assessment of intensity, relatedness and expectedness will be made by the Principal Investigator at each research site for all serious adverse events. Suspected unexpected serious adverse reactions (SUSARs) will be reported to the coordinating centre within 24 hours, and discussed at each scheduled DMC meeting. SUSARs will be additionally reported to the trial Sponsor within 5 days and the Research Ethics Committee within 24 days. As there is a potential for
*ad hoc* adverse events to be more readily identified in the intervention arm, the Principal Investigator at all research sites (irrespective of randomisation status) will undertake an additional proactive review of all participants’ hospital admissions, GP consultations and deaths during the study period and at the end of study follow-up. This will help identify differences in adverse event rates between study arms.

An adverse event will be deemed to have occurred where a change to the prescribed medication is required to counter a change in medication made at the initial intervention (patient-facing review) appointment. An adverse event will be considered expected if a) an adverse drug reaction (ADR) has occurred (i.e. consistent with the WHO definition of ADR, listed in the British National Formulary (BNF)
^
27
^ as common or very common, and the drug or an interacting drug has been changed as a consequence of the IMPPP intervention), b) worsening of the drug clinical indication has occurred (i.e. where the indication is listed in the BNF, and the drug or an interacting drug has been changed as a consequence of the IMPPP intervention), or c) there is an adverse change in patient behaviour considered by the clinician to be consistent with that expected as a direct consequence of the intervention. Unexpected events will include ADRs considered uncommon, rare or unlisted in the BNF, or an intensity of event greater than that clinically expected, or a worsening of clinical condition despite a clinically appropriate drug change.

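### The stated adverse-event definition is narrower than the events the same safety section sets out to review and classify

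*Protocol article*

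**What the plan says.** All of the relevant wording is in the protocol article, under Safety reporting, apart from two outcomes in Table 1.

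- **Definition.** "An adverse event will be deemed to have occurred where a change to the prescribed medication is required to counter a change". The change to be countered is then specified as "a change in medication made at the initial intervention (patient-facing review) appointment". No other definition of an adverse event appears in the article.
- **Serious events.** "Serious adverse events will be monitored, recorded and reported in accordance with the Good Clinical Practice (GCP) guidelines and the" sponsor's own policy. The site's Principal Investigator judges severity, relatedness and expectedness for every serious event.
- **Background expectation.** The section opens by saying that, in this population, "new diagnoses, hospital admissions and death are to be anticipated".
- **Proactive review.** Every site, in either arm, is to review all participants' "hospital admissions, GP consultations and deaths during the study period and at the end of study follow-up". The stated purpose is: "This will help identify differences in adverse event rates between study arms".
- **Expectedness.** Criteria a and b concern reactions, or worsening of the indication, where the drug or an interacting drug was altered because of the intervention. Criterion c applies where "there is an adverse change in patient behaviour considered by the clinician to be consistent with that expected as a direct consequence of the intervention". The unexpected category includes greater intensity than foreseen and clinical worsening despite an appropriate drug change.
- **Outcomes.** Table 1 lists all-cause mortality (GP records) and medication-related admissions (HES) as patient and medicines safety outcomes.

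**The concern.** The definition sets two conditions: a medication change must be needed to counter an earlier one, and the earlier one must have been made at the initial review appointment. Both relate poorly to severity. A fatal event leaves no medication to adjust. A fracture or stroke may not be answered by any prescribing change. A mild, reversible effect that is dealt with by altering the drug qualifies easily.

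An investigator who applies the sentence as written during the review of deaths and admissions could therefore set aside some of the most serious events and keep the milder ones. Another investigator might rely on the GCP reference and record them all. What is at stake is consistent ascertainment between sites, and which events receive an individual relatedness assessment. This matters for oversight because suspected unexpected serious adverse reactions are the event class that the article says is discussed at each scheduled Data Monitoring Committee meeting.

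**Working it through.** No arithmetic applies; the check sets each part of the safety text against the two conditions in the definition.

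1. **Death after a medication change made at review.** The proactive review covers it. The definition does not, because no countering change can follow.
2. **Irreversible harm that is not answered by a medication change.** The review covers it if it led to an admission or consultation. The definition does not. The definition should be read fairly here: any change to the prescribed medication counts, so stopping a drug or altering its dose would meet it, not only issuing a new prescription. The gap is confined to harms where no such change is needed.
3. **Harm from an intervention-related change not made at the initial appointment.** Criteria a and b cover it, since they turn on a drug having been altered because of the intervention, with no limit to one appointment. The definition does not.
4. **Adverse behaviour change.** Criterion c classes this as an expected adverse event and mentions no countering medication change. The definition requires one.
5. **Clinical worsening, or greater intensity than foreseen.** The unexpected category covers both without mentioning a countering change. The definition requires one.
6. **Comparison between arms.** The purpose given for the review is to compare adverse event rates. Control patients have no trial review appointment, so on the literal definition a control patient cannot have an adverse event, and the comparison has no common basis.

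Expectedness rules ordinarily sort events that already count as adverse events. In items 3 to 5 the sorting rules are worded more widely than the definition of what is to be sorted. In items 1, 2 and 6 the review is aimed at events that the definition would largely not admit. The mismatch lies between statements that are present in the article; it does not depend on detail the article leaves out.

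**The case against.** The strongest reply is that the sentence says when an adverse event is deemed to have occurred and does not say that nothing else counts. A reader might infer that deaths and irreversible harms can never be serious adverse events or SUSARs. The documents do not support that. Serious events have their own sentence, which points to GCP and to a sponsor policy that is not shown, and it is not tied in words to the narrow definition. Requiring a relatedness judgement for every serious event also suggests wider capture, since relatedness would be largely settled if each event had to counter a review change. This part of the objection stands.

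It also stands that mortality and medication-related admissions are collected as outcomes without reference to the definition, so deaths will be counted by arm. Those counts do not, however, supply an individual relatedness assessment or prompt reporting.

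The reply can add that criteria a to c merely classify events that already meet the definition, so there is little conflict. That reading is possible for a and b if every change is made at the initial appointment, and c does not rule out a countering change. But it needs limits that the text does not state, and it leaves the purpose of the proactive review unexplained.

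A reader might also infer that the intervention involves staged later changes whose harms are excluded. The article does not describe such changes; intervention detail is in an appendix that is not shown. The word initial, beside the wider wording of criteria a and b, only leaves room for them.

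Finally, the full protocol may define these terms completely. That would explain missing detail, but not a stated rule that conflicts with its neighbours.

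**Conclusion.** The point holds as an internal inconsistency. The only adverse-event definition in the article is narrower than the events its safety section reviews, classifies and intends to compare between arms. Applied as written in the planned site review, it would misclassify deaths, harms needing no countering medication change, and harms from intervention-related changes made outside the initial appointment.

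It is not established that such events go unrecorded, that they cannot be serious adverse events or SUSARs, or that the Data Monitoring Committee will not see them. Nor can a number be put on the effect: the documents give neither an event rate nor the share of events related to review changes. The conclusion assumes that sites work from the definition as published and that the sponsor's policy does not already override it. It merits correction because it affects safety ascertainment and is cheap to put right.

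**What to change.** Reconcile the definition with the serious-event statement, the proactive review and the expected and unexpected categories, so that a countering medication change arising from the initial appointment is no longer a necessary condition. In practice:

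- record every death, unplanned admission and other untoward event found in the planned review, in both arms;
- then assess relatedness to the intervention as a separate step;
- keep the need for a countering medication change as one recorded attribute of the event;
- state explicitly how the trial definition relates to the sponsor's policy for serious events.

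The cost is a wording amendment and a change to the event form. The site review of admissions, consultations and deaths is already planned, including at the end of follow-up, which the article expected to finish by July 2023, after its publication in November 2022. The small downside is more events to record and assess.
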